### Reporting of Serious Adverse Events

Every serious adverse event occurring throughout the trial must be notified to the AMANET by the investigator as **soon as he is alerted to it**, i.e., **within 24 hours of being alerted**, even if the investigator considers that the adverse event is not related to treatment. The dully completed SAE form should be submitted **within 5 working days**, and the same must also be transmitted to the chair of the DSMB bearing nor personal identifiers or treatment allocation.

Any relevant information concerning the adverse event that becomes available after the SAE report form has been sent (outcome, precise description of medical history, results of the investigation, copy of hospitalisation report, etc.) should be forwarded as soon as possible to the Sponsor and the chair of the DSMB within 24 hours from the investigator learning of it. The anonymity of the subjects shall be respected when forwarding this information.

| **Study Contact for Reporting of a Serious Adverse Event** | |
| --- | --- |
| All three of the contacts listed below must be informed of each SAE | |
| **Study Contact at AMANET for Reporting Serious Adverse Events** | |
| **[name]**, BSc. MB ChB, Clin Research, DHTM  Clinical Trials Coordinator,  [name],  [name]  Dar es salaam, Tanzania  [contact] [contact]  E-mail: [[contact]](mailto:[contact]) | |
| **Local safety monitor** | **Clinical Monitor** |
| To be named | **[name],** MD, MPH  Malaria Research and Training Center (MRTC)  Department of Epidemiology of Parasitic Diseases (DEAP) Faculty of Medicine, Pharmacy and Dentistry, (FMPOS)  University of Mali; [name] |
|  | |

## Regulatory requirements

In order to comply with current regulations on serious adverse event reporting to Health Authorities the investigator shall document accurately the event, respect notification deadlines, provide AMANET with all necessary information and, if requested, to give access to source documents.

The Investigator shall further inform the relevant Health Authorities as soon as possible, of any serious adverse event likely to be related to the product (or to the trial). AMANET shall also inform the Authorities of any trial discontinuation and specify the reason for discontinuation.

The principal investigator will inform the other investigators and the Ethics Committee of the occurrence of any serious adverse drug reaction.

## Blood sampling

A blood sample, to be taken as soon as possible, may be requested in case of a serious adverse event if it might help in determining the cause of the SAE. An appropriate blood volume in a correct container would be obtained for relevant tests.

## Lost to Follow-up Procedures

If a participant fails to appear for a follow-up examination, intensive efforts to visit them at home will be undertaken to recall them or at least to determine their health status. These efforts will be documented in the subject’s CRF and source documents.

## Specific case: Diagnosis and treatment of Malaria cases

### Diagnosis

Although symptoms of uncomplicated malaria can be rather non specific, in this study, malaria diagnosis should be confirmed by detection of parasitaemia. However, in high transmission areas such as Balonghin, where the immunity is high, asymptomatic parasitaemia is common. The following clinical signs significantly associated to malaria have been observed and are widely acceptable for suspicion of malaria:

(a) Axillary temperature 37.5° C;

(b) Axillary temperature < 37.5° C, but with history of fever within the preceding 24 hours;

(c) History of illness with other signs than fever,

Patients presenting with these features will be investigated for malaria, and the decision to provide treatment will be at the discretion of the clinical investigators.

### Malaria case management

- **Uncomplicated Malaria Cases**

Any participant diagnosed as an uncomplicated malaria case will receive Coartem 20/10mg (artemether 20mg-lumefantrine 120mg) using a 4-dose regimen (16 tablets, 320 mg artemether and 1920 mg lumefantrine, given over 2 days) as oral first-line treatment. Therapy is delivered over 2 days with the dosage based on the patient’s body weigh; detailed instructions on dosing is provided in the manual of SOP under treatment of malaria at time 0, 8, 24 and 48 hours.

- **Severe Malaria Cases**

The treatment is based on quinine salts delivered by IV slow perfusion as follows:

- A loading dose of 20 mg dihydrochloride salt/kg of body weight (loading dose) 1 diluted in 10 ml isotonic fluid/kg by IV infusion over 4 hours;
- then 8 hours after the start of the loading dose, give a maintenance dose of quinine, 10 mg salt/kg, over 4 hours. This maintenance dose should be repeated every 8 hours, calculated from the beginning of the previous infusion, until the patient can swallow,
- then Coartem at the same dosage regimen as for uncomplicated malaria.

Response should be monitored by frequent clinical examination including recording of fluid balance, temperature, pulse, respiratory rate and depth, level of consciousness, blood pressure, jugular venous pressure, and parasitaemia (in blood films) every 4–6 hours for the first 48 hours.

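### Section 13.8.2 states one fixed 16-tablet Coartem course for any participant with uncomplicated malaria, then says dosage goes by body weight; the fixed total should come out

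*Protocol*

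**What the plan says.** Protocol section 13.8.2 (Malaria case management) opens with a rule for everyone: "Any participant diagnosed as an uncomplicated malaria case will receive Coartem 20/10mg", which it describes in brackets as 20 mg artemether with 120 mg lumefantrine. The same sentence sets the course: "using a 4-dose regimen (16 tablets, 320 mg artemether and 1920 mg lumefantrine, given over 2 days".

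The next sentence reads differently: "Therapy is delivered over 2 days with the dosage based on the patient" (the text goes on to name body weight), and "detailed instructions on dosing is provided in the manual of SOP under treatment of malaria at time 0, 8, 24 and 48 hours".

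For severe malaria, quinine is written per kilogram: "A loading dose of 20 mg dihydrochloride salt/kg of body weight", and after that "give a maintenance dose of quinine, 10 mg salt/kg, over 4 hours". Once the child can swallow, the instruction is "then Coartem at the same dosage regimen as for uncomplicated malaria".

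Section 13.8.1 (Diagnosis) adds that "the decision to provide treatment will be at the discretion of the clinical investigators". That concerns whether to treat, not how much to give.

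The title and the inclusion criteria restrict the trial to children aged 12 to 24 months. The protocol gives no weight bands, no mg/kg target for Coartem and no body weights. It does not describe the 16 tablets as a maximum, an example or a course for a particular weight.

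**The concern.** A total stated for any participant is a complete instruction on its face: a reader can act on it without going further. The sentence after it gives a different kind of instruction, one that varies from child to child. The protocol does not say which of the two prevails. The step-down after quinine points back to this paragraph rather than to the SOP, so severe cases meet the same choice.

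What is at stake is the amount of an antimalarial given to toddlers in a trial whose primary objective is safety. The paragraph is likely to be used. The planned period, March 2007 to February 2008, covers the whole June to October transmission peak, and the Epidemiology section says that under-fives have multiple episodes in those months.

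**Working it through.** **Inputs, all from section 13.8.2:** tablet contents 20 mg artemether and 120 mg lumefantrine (the bracketed description); 16 tablets in total; 4 doses, at 0, 8, 24 and 48 hours.

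**1. Reproduce the stated totals.**
- Artemether: 16 × 20 mg = 320 mg, as stated.
- Lumefantrine: 16 × 120 mg = 1920 mg, as stated.

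The fixed course is therefore internally consistent at 20/120 mg per tablet. At the printed label of 20/10 mg, lumefantrine would be 16 × 10 = 160 mg, which does not match 1920 mg. The label is the slip.

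**2. Amount per dose.** The protocol does not say that the doses are equal; assume that they are.
- Tablets: 16 / 4 = 4 per dose.
- Artemether: 4 × 20 = 80 mg per dose.
- Lumefantrine: 4 × 120 = 480 mg per dose.

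**3. When do the two sentences agree?** Let *k* be the number of tablets per dose that the weight rule gives a child. The weight-based course is 4*k* tablets, and 4*k* = 16 only if *k* = 4. The sentences are compatible for the whole trial only if every child aged 12 to 24 months falls in a band with *k* = 4. In that case the weight sentence would make no difference to any participant.

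**4. What the fixed total would mean by weight, if it were followed.** The protocol gives no weights, so 7 to 16 kg is an assumed range for illustration.

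| Assumed weight | Artemether per dose | Lumefantrine per dose | Artemether per course | Lumefantrine per course |
| --- | --- | --- | --- | --- |
| 7 kg | 80/7 = 11.4 mg/kg | 480/7 = 68.6 mg/kg | 320/7 = 45.7 mg/kg | 1920/7 = 274 mg/kg |
| 10 kg | 8.0 mg/kg | 48.0 mg/kg | 32.0 mg/kg | 192 mg/kg |
| 16 kg | 80/16 = 5.0 mg/kg | 480/16 = 30.0 mg/kg | 320/16 = 20.0 mg/kg | 1920/16 = 120 mg/kg |

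The spread is 16/7, about 2.3-fold. This shows only that a constant tablet count is not dosing by body weight. It does not show which mg/kg figure is right, because the documents give no target, and it does not show that any child would be given the fixed course.

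**The case against.** The strongest reply is that the paragraph answers its own question. The weight sentence comes after the tablet total, is the more specific on how to dose, and hands the detail to the SOP manual. Section 21 (Appendices) lists the vaccine trial SOPs as a protocol annex. A clinician who reads to the end of the paragraph would probably dose by weight. This is also background care: neither the study vaccine nor the allocation, endpoints or analysis is involved.

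Most of that stands, and it limits the point. It does not remove it, because the total is stated without qualification for any participant and nothing says that the SOP overrides it.

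Three stronger readings are tempting, and the documents do not support them:

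- **That the protocol fixes 4 tablets per dose for every child, or prescribes an overdose.** The same paragraph says that dosage varies with weight. The weight rule is in a document not at hand, so no misdosing can be shown.
- **That the malaria-treatment SOP does not exist.** None of the 13 SOPs listed in section 18.4 carries that title, but the list is not exhaustive: section 16.5 cites data-management SOPs and section 18 cites quality-management SOPs, and neither appears there. Malaria dosing could also sit under the listed SOP on medical care of the volunteers.
- **That a child dosed by weight would be a protocol deviation.** The protocol itself points to the SOP for dosing, so following that SOP can be read as compliance.

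**Conclusion.** The inconsistency is real and can be read directly from section 13.8.2. An unqualified course of 16 tablets stands beside a weight-based rule, and the two agree for all participants only if every child's weight-based dose is 4 tablets. Both treatment paths, uncomplicated malaria and the step-down after quinine, are affected.

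The severity is modest. The SOP reference suggests that weight-based dosing is what was meant, and no dosing consequence can be quantified without that SOP. No endpoint, sample size, power figure or analysis changes. The point deserves correction because it concerns a treatment instruction for 12-to-24-month-olds and the ambiguity can be removed with one edit.

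The conclusion rests on the wording of the paragraph and on the assumption of equal doses. It does not rest on the assumed weights in the table.

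**What to change.** In section 13.8.2:

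- Delete the fixed total (the tablet count and the two milligram totals).
- State that the number of tablets per dose is set by body weight according to the malaria-treatment SOP, and identify that SOP.
- Before the change is made, have the responsible clinician check the protocol paragraph against the SOP. No dose is proposed here.
- State that the same weight-based rule applies both to uncomplicated cases and to Coartem after quinine in severe cases.
- Correct the tablet strength in the same sentence from 20/10 mg to 20/120 mg.

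The cost is a text correction to one paragraph and one check against the SOP. Design, sample size and analysis are untouched.

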# Primary evaluation criteria

## Definition of the Criterion

The reactogenicity and the safety shall be assessed on the following criteria:

1. Immediate reactogenicity (within 60 minutes, with emphasis on allergic reactions),
2. Local and systemic reactogenicity during the 7 days following each vaccination.
3. Any unsolicited adverse events (AE) occurring outside scheduled visit times, up to one month after the third vaccine dose and requiring a physician visit
4. Any serious adverse events (SAE) whenever they occur during the trial period (from first visit to last visit). The relationship with the vaccine must be determined by the investigator, using the following definitions: **not related, possibly related, probably related, definitely related.**
5. Biological safety, assessed four weeks after each injection, in relation to the baseline data profile on the following:

RBC, haemoglobin, haematocrit, platelets, WBC, Liver enzymes (SGOT, GPT, total bilirubin) and creatinine.

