| **Primary**  **Evaluation Criteria** | The primary endpoints are measures of the safety and reactogenicity of the vaccine as determined by:   1. Occurrence of solicited symptoms during a 7 day follow-up period after each vaccination (day of vaccination and 6 consecutives days) 2. • Occurrence of unsolicited symptoms during a 28 day follow-up period after each vaccination 3. • Occurrence of serious adverse events throughout the study period |
| **Secondary Evaluation Criteria** | 1. **Humoral response to vaccine antigens:**   Post vaccination levels of IgG, IgA and IgM, expressed in arbitrary units (ng/ml), relative to the pre-vaccination level (D0): D28/D0, D56/D0, D84/D0, D168/D0, and D365/D0.   1. **Cellular immune response to vaccine antigens:**   The number of cells producing IFNγ by Elispot expressed in number of spots /106 cells |
| **Exploratory Evaluation Criteria** | **To evaluate IgG ability to recognise the native protein on Merozoite by using WB**   - **Parasite inhibition by ADCI (SGI %) on D0, D84, D168 and D365. (only if isotype study shows the production of MSP3 specific cytophilic Abs in > 30% of volunteers)** |
| **Statistical Methods** | The analysis shall be descriptive  The final analysis is planned 1 month post Dose 3 to evaluate whether the safety GO/No GO criteria are met to proceed to a phase 2b in. An annex safety analysis will be performed at the end of the study, 9 months post Dose 3. |

| Study phases | Screening | Vaccination Phase (Double blind) | | | | | | | | | | Follow up (Single blind) | | |
| --- | --- | --- | --- | --- | --- | --- | --- | --- | --- | --- | --- | --- | --- | --- |
| Clinic Visit | **V1** | **V2** |  | **V3** | **V4** |  | **V5** | **V6** |  | **V7** | **V8** | **V9** |  | **V10** |
| **Home visits1** |  |  | **HV1-5** |  |  | **HV6-10** |  |  | **HV11-15** |  |  |  | **HV16-21** |  |
| **Trial Timelines (Days,)** | **D-28** | **D0** | **D1-D5** | **D6** | **D28** | D29-D35 | **D36** | **D56** | **D57-D62** | **D63** | **D84** | **D168** | **D196-D337** | **D365** |
| **Time Windows (Days)** |  |  4 D |  |  |  4 D |  |  |  4 D |  |  |  4 D |  7 D |  7 D |  14 D |
| **Study procedures** |  |  |  |  |  |  |  |  |  |  |  |  |  |  |
| Screening consent |  |  |  |  |  |  |  |  |  |  |  |  |  |  |
| Study Consent |  |  |  |  |  |  |  |  |  |  |  |  |  |  |
| Check of inclusion /non Inclusion Criteria |  |  |  |  |  |  |  |  |  |  |  |  |  |  |

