# Trial Objectives

## Primary Objective

**To assess the safety and reactogenicity** of 3 doses of 15 µg and 30 µg MSP3 LSP adjuvanted in Aluminium hydroxide given at D0, D28 and D56 in healthy children 1-2 years old in Burkina Faso on the following:

1. Immediate reactogenicity (within 1 hour, with emphasis on allergic reactions),
2. Local and systemic reactogenicity during the 7 days following the vaccine administration(day of vaccination and 6 subsequent following days)
3. Unsolicited adverse events occurring within 28 days following each vaccination
4. Serious adverse events (SAE) throughout the study period.

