|  | **SCREENING** | | | | | | | **VACCINATION** | | | | | | | | | **LONG TERM SAFETY FOLLOW UP** | | |  |
|  |  | | | | | | | **DOUBLE-BLIND PHASE** | | | | | | | | | **SINGLE-BLIND PHASE** | | |  |
|  |  | | | | |  |  |  |  | |  | |  | |  | |  |  | |  |
| **BS;** Blood Sample. **Vacc;** Vaccination. | | | | | | | | | | | | | | | | | | | | |
|  | | | | | | | | | | | | | | | | | | | | |

- Double blind (observer blind, participant blind), randomized, controlled, dose escalation, Age de-escalation, phase Ib study
- One study centre,
- Two parallel groups
- Group 1: 23 subjects (15 subjects receiving MSP-3 vaccine 15 µg and 8 subjects receiving Hepatitis B vaccine).
- Group 2: 22 subjects (15 subjects receiving MSP-3 vaccine 30 µg and 7 subjects receiving Hepatitis B vaccine)
- Immunization schedule will be 0, 1, and 2 months for all cohorts and provisionally as following for each group:
  - Study days 0, 28 and 56 for group 1
  - Study days 14, 42, 70 for group 2
- Vaccinations of groups 1 and 2 will be staggered: immunization in group 2 will start 2 weeks after group 1. This interval may be extended if deemed necessary due to SAEs or other safety concerns.
- Randomization will be done for each group at the times of first vaccinations.
- Route of inoculation will be by subcutaneous injection into right or left deltoid (alternately).
- Each child will be observed for at least 60 minutes after vaccination to evaluate and treat any acute adverse events (AEs)
- Study duration will be approximately 13 months per subject.
- Seven (7) day follow-up period for solicited adverse events (day of vaccination plus 6 subsequent days)
- Twenty eight (28) day follow-up period for unsolicited adverse events (Vaccination day plus 27 subsequent days)
- Follow-up of serious adverse events (SAE’s) for 12 months after the first dose of study vaccine (9 months after dose 3)
- At the end of the follow-up period for unsolicited AEs (i.e., one month after the third dose), subjects will be followed by field workers at home at monthly intervals to record SAEs.
- Data collection: conventional Case Report Form (CRF).

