### Vaccination and serological schedule

Scheduled clinic visits are planned at day -28, 0, 6, 28, 36, 56, 63, 84, 168 and 365. Three vaccine doses will be administered by subcutaneous injection (day 0, 28 and 56). As shown in the flow chart (see page 9), participants will be monitored for the hour following vaccination, then a field worker will visit them at home on each of the 5 days following the injection. The patient will come back to the clinic at the 6th day following each immunization to be assess by a study clinician. Six serological blood sampling points have been planned on days 0, 28, 56, 84, 168 and 365.

Biological evaluations will also be done on days -28, 0, 6, 28, 36, 56, 63, 84 and 365. Apart from these standard examinations, other tests may be performed if deemed necessary.

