## Unsolicited symptoms

Unsolicited symptom is defined as any adverse event (AE) reported in addition to those solicited during the clinical study. Also any “solicited” symptom with onset outside the specified period of follow-up for solicited symptoms will be reported as an unsolicited adverse event.

Unsolicited symptoms will be recorded from the first dose of vaccination to 30 days post third dose.

For the unsolicited symptoms, intensity will be assessed as follows:

| Mild | Easily tolerated by the subject, causing minimal discomfort and not interfering with everyday activities. |
| --- | --- |
| Moderate | Sufficiently discomforting to interfere with normal everyday activities. |
| Severe | Prevents normal, everyday activities. |

Outcome and causal relationship will be assess as described in section 13.4.2.3 and 13.4.2.4

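### Section 14.1 restricts the unsolicited part of the primary safety criterion to events outside scheduled visits that need a physician, contradicting the synopsis, the objectives and section 14.2.2

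*Protocol*

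**What the plan says.** **Unsolicited events.** Section 2.1 sets the objective as "Unsolicited adverse events occurring within 28 days following each vaccination". The synopsis uses the same 28 days, and section 3 spells them out as "Vaccination day plus 27 subsequent days". None of these restricts events by setting or by need for care. Section 14.1 item 3 narrows the criterion to "Any unsolicited adverse events (AE) occurring outside scheduled visit times, up to one month after the third vaccine dose and requiring a physician visit". Section 14.2.2 takes in any adverse event that is not solicited, provides a mild grade, and gives another window: "Unsolicited symptoms will be recorded from the first dose of vaccination to 30 days post third dose". Section 13.4.2.4 (Assessment of Outcome) also uses 30 days.

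**Solicited events.** The synopsis and sections 2.1 and 3 define the window as the vaccination day plus six days. Section 14.2.1.1 (local reactions) refers to D1 and D7, and section 14.2.1.2 (systemic reactions) to D1 to D6. Section 5.2.4 says "The patient will come back to the clinic at the 6th day following each immunization", and section 5.2.5 also places the final assessment on day 6. Yet section 5.2.4 also says "Scheduled clinic visits are planned at day -28, 0, 6, 28, 36, 56, 63, 84, 168 and 365", and the flow chart agrees with those dates.

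**Serious adverse events.** Section 3 states that, from one month after the third dose, "subjects will be followed by field workers at home at monthly intervals to record SAEs". The flow chart timeline ends "D84 | D168 | D196-D337 | D365", with the six monthly home visits (HV16 to HV21) placed only in the D196 to D337 column.

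**The concern.** The trial's purpose is safety, and the analysis about one month after dose 3 exists to decide whether the safety criteria for phase 2b are met (synopsis, sections 5.2.3 and 6.3). The section that formally defines the primary criterion should therefore count the same events as the objective. Section 14.1 does not: it adds two conditions found nowhere else. An analyst following 14.1 and one following section 2.1 would report different numbers for the same endpoint, and the choice could be made after the data are seen.

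The schedule conflicts raise a smaller question of the same kind. If follow-up differs from dose to dose, reactogenicity by dose number is not measured in the same way each time. The protocol's own account of the phase 1a trial links local tolerance to injection number.

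**Working it through.** Days count from each child's first dose on the nominal schedule (doses at D0, D28 and D56), ignoring visit tolerances.

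**1. Which unsolicited events count**

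| Place | Events | Window |
|---|---|---|
| Synopsis, 2.1 | all | 28 days after each dose |
| Section 3 | all | day 0 to 27 |
| 14.1 item 3 | outside scheduled visit times and needing a physician | to one month after dose 3 |
| 14.2.2 | any, mild to severe | dose 1 to 30 days after dose 3 |
| 13.4.2.4 | non-serious | 30 days post-vaccination |

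The two conditions in 14.1 are joined, so an event must meet both. The physician condition has the clear effect: a mild event that needs no physician is in scope under 2.1, 3 and 14.2.2, and out of scope under 14.1. No document gives the share of such events. For scale, with 15 children per MSP3 arm (section 16.2), one child whose only unsolicited event is of this kind moves the arm's rate by 1/15 = 6.7 percentage points.

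**2. The 28-day and 30-day windows**

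- Day 0 to 27 gives D0–D27, D28–D55 and D56–D83, which is continuous.
- Thirty days after dose 3 gives 56 + 30 = D86.
- Recording therefore differs only after dose 3: D83 against D86.
- Read per dose, 30 days after dose 1 runs to D30 and overlaps dose 2 (D28).
- Section 6.3 places the final analysis immediately after D84. The 28-day window has closed by then; the 30-day window has not.

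**3. Solicited events**

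- Clinician visit, days after dose: 6 − 0 = 6; 36 − 28 = 8; 63 − 56 = 7. The window ends on day 6.
- Home visits, five after each dose: D1–D5 (5 days), D29–D35 (7 days), D57–D62 (6 days). The flow chart footnote calls them daily.
- After dose 1, five home visits and the D6 clinic visit cover all six post-dose days of the window. After dose 2 those days are D29–D34, and after dose 3 D57–D62. In both cases at most five of the six have a home visit and the clinic visit comes later, so at least one day has no contact.
- On the flow chart's numbering, D7 in 14.2.1.1 is a day beyond the window. D1 to D6 in 14.2.1.2, with the 60-minute observation, fits it.

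**4. SAE home visits**

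- HV16–HV21 is six visits; (337 − 196)/5 = 28.2 days apart, so they fill D196–D337 exactly. With HV1–HV15 this makes the 21 home visits stated in section 5.2.3, so the flow chart is self-consistent and the conflict is with section 3.
- From D84 to D168 is 84 days; from D84 to D365 is 281 days; 84/281 = 30% without a scheduled contact.
- For first doses between 1 and 31 March 2007 (an assumption from the planned March start), D84 falls between 24 May and 23 June, and D168 between 16 August and 15 September. The protocol gives the transmission peak as June to October.

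**5. Stated power**

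Section 16.2 gives the chance of at least one event among 14 children as 1 − (1 − p)^14: 0.897 at 15%, 0.804 at 11% and 0.948 at 19%. This reproduces the stated 90%, 80% and 95%. It concerns systemic reactions and SAEs, so the 14.1 restriction on unsolicited events does not alter it.

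**The case against.** The best defence is that the data would be collected anyway. Section 13.4.2 requires all adverse events to be documented, whether observed or reported. Section 14.2.2 records any of them, and section 5.2.10 tabulates all unsolicited events after doses 1 and 2 for the DSMB. The analysis is descriptive (16.4). This stands, and it makes the defect one of definition rather than lost data. The definition still decides which events enter the primary result.

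Several stronger readings are tempting, but the documents do not support them:

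- A reader might infer that every event found at the 7 clinic and 15 home contacts from D0 to D84 is excluded, and so most events. Item 3 speaks of when an event occurs, not where it is found. An event that starts between visits and is reported at one still occurred outside visit time.
- A reader might infer that reactions first seen at D36 or D63 become unsolicited, biasing reactogenicity after doses 2 and 3 downwards. Section 14.2.2 reclassifies by onset, 13.4.2 records date and duration, and the flow chart marks solicited recording at both visits. Later visits could equally lengthen ascertainment, so no direction of bias is shown.
- A reader might count the D36 and D63 blood draws as outside the window. The seven-day window governs symptoms; 14.1 item 5 assesses biological safety four weeks after each injection.
- A reader might conclude that SAEs go uncollected in the malaria season. Sections 13.4.2.1 and 13.4.3 cover SAEs throughout the trial, families are told to report illness at any time (5.2.3), and scheduled contact resumes at D168, within the peak.

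**Conclusion.** The contradiction in 14.1 item 3 is established by the text and changes which events count in the primary safety result. The loss concerns mild events that need no physician, and its amount cannot be determined from the protocol. The 28- against 30-day conflict is small: three days of recording after dose 3, plus overlap of per-dose windows.

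The other two conflicts are lesser matters of reconciliation. Solicited follow-up is not the same after each dose (clinician on day 6, 8 or 7; at least one day of the window without contact after doses 2 and 3), with no demonstrated direction of bias. The home visits for SAEs stated in section 3 are absent from the flow chart between D84 and D168. That is 30% of the time from D84 to D365 and lies partly within the transmission peak if dosing starts in March. What is missing there is scheduled contact; the duty to report SAEs is not affected. The sample-size statement is unaffected.

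**What to change.** **Main change.** In 14.1 item 3, delete the condition about scheduled visit times and the condition about needing a physician. Use one unsolicited window, the 28 days (day 0 to 27) of the objectives and section 3, in 14.1, 14.2.2 and 13.4.2.4. This is wording only and adds no data collection.

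**Solicited follow-up.** Reconcile the flow chart and its footnote with sections 5.2.4, 5.2.5, 14.2.1.1 and 14.2.1.2, so that home visits, clinician visit and symptom window fall on the same post-dose days after every dose. The sponsor should settle which days apply; the cost is a change of text and chart dates.

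**SAE home visits.** Reconcile section 3, the flow chart and its footnote, and the total of 21 home visits in section 5.2.3. If the flow chart stands, section 3 is reworded at no cost. If section 3 stands, two monthly visits are added between D84 and D168 (84 + 28 = D112 and 112 + 28 = D140). That is up to 2 × 45 = 90 home contacts, and the stated total becomes 21 + 2 = 23.
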